***6.2.3. Secondary Functional Outcome Objectives***

• To test the effect of atomoxetine for the following measures compared to placebo:

− Habits Timeline Followback (TLFB) (Alcohol, Nicotine, Caffeine, Marijuana, and Drugs): the incidence of use for each of the following habits separately: alcohol, nicotine, caffeine, marijuana, and drugs as measured by the mean change

− Fagerstrom Test for Nicotine Dependence

− Social Adaptation Self-Evaluation Scale (SASS)

− Driving Behavior Survey Self-Report

− Driving Behavior Survey - Other Report

− Behavior Rating Inventory of Executive Function-Adult Version Self

Report (BRIEF-A)

− Epworth Sleepiness Scale

• To assess baseline smoking status as a predictor of response (a 25% decrease from baseline on the CAARS-Inv:SV total ADHD symptom score) and strong response (a 40% decrease from baseline on the CAARS-Inv:SV total ADHD symptom score ) to atomoxetine treatment compared with placebo.

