***12.2.6. Primary Outcome and Methodology***

The primary summary measure, the CAARS-Inv:SV total ADHD symptom score as well as the Inattention subscale score, and Hyperactivity-Impulsivity subscale score, will be analyzed using a restricted maximum likelihood (REML)-based, mixed model repeated measures (MMRM) technique. The model will include the fixed, categorical effects of treatment, investigator, visit, and treatment-by-visit interaction as well as the continuous, fixed covariates of baseline (last of scores at Visit 1 and Visit 2) score and baseline score- by-visit interaction. The following covariance structures will be fit to the model: unstructured, heterogeneous toeplitz, heterogeneous autoregressive, heterogeneous compound symmetry and simple. The correlation structure converging to the best fit as measured by Akaike's Information Criterion will be used as the primary analysis. The Kenward-Roger approximation will be used to estimate denominator degrees of freedom. Significance tests will be based on least-squares means and Type III sum-of-squares. Analyses will be implemented using SAS PROC MIXED. The primary comparison is

the contrast between treatments at Visit 6 (12 weeks post-baseline). Secondary evidence of efficacy from the primary analysis will be based on the main effect of treatment and

the treatment-by-visit interaction terms from the MMRM analysis. This measure will be summarized separately during Study Period III. All statistical tests will be two-sided and will be conducted at the 5% significance level.

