Variables 1-5 will be summarized for Study Period II using the last of Visits 1 and 2 as baseline and Visits 3-6 as the post-baseline visits. Variable 1a will be analyzed during Study Period II using a restricted maximum likelihood (REML)-based mixed effects model, repeated measures technique as defined for the primary efficacy analysis. This variable will be analyzed over the course of Study Period II using a contrast from the repeated measures mixed effects model at the final post baseline visit. Additionally,

visit-wise efficacy will be assessed using contrasts from this model at each post baseline

visit. This variable will be summarized separately by visit during Study Period III.

Variables 2.a through 2.n will be analyzed using a fixed-effects analysis of covariance (ANCOVA) model with terms for baseline score, treatment, and investigator. These variables will be summarized separately during Study Period III.

Variables 3-6 will be compared across treatment groups during Study Period II and separately during Study Period III using a Fisher’s Exact Test.

Time to response and time to remission will be compared across treatment groups during Study Period II using the Kaplan-Meier Product limit estimator, with the test for treatment difference being based on the log-rank test.

Correlation between the AAQOL-29 total score and the CAARS-Inv:SV total ADHD symptom score will be computed using Pearson’s correlation co-efficient to assess the relationship between these two measures.

A Fisher’s Exact Test will be used to assess baseline smoking status as a predictor of response (a 25% decrease from baseline on the CAARS-Inv:SV total ADHD symptom score) and strong response (a 40% decrease from baseline on the CAARS-Inv:SV total ADHD symptom score ) to atomoxetine treatment compared with placebo. If sparse data exists, a Chi-Squared analysis may be used instead.

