***12.2.10. Subgroup Analyses***

The subgroup analyses will include analyses between each subgroup of patients as well as statistical models that test for subgroup effects and treatment by subgroup interaction.

Subgroups of patients for efficacy analyses will include investigational site, prior- stimulant-use strata, ADHD subtype, gender, and age.

For investigational site subgroup analyses (pooled as described in Section 12.2.1.1), changes in CAARS-Inv-SV total ADHD symptom score will be assessed using an ANCOVA model, including terms for baseline, treatment, subgroup, and the treatment- by-subgroup interaction. If the interaction is statistically significant at the 0.10 level, then the potential causes of the interaction will be investigated.

The incidence of treatment-emergent adverse events (TEAE) will be summarized by the following subgroups; investigational site, prior-stimulant-use strata, ADHD subtype, gender, and age.

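### The baseline-smoking objective is analysed only on the 25% and 40% response cuts of CAARS-Inv:SV, with no full-scale treatment-by-smoking analysis specified

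*Protocol*

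**What the plan says.** Section 6.2.3 lists the objective: "To assess baseline smoking status as a predictor of response (a 25% decrease from baseline on the CAARS-Inv:SV total ADHD symptom score" and, as a second outcome, strong response at a 40% decrease. Both are to be assessed for atomoxetine compared with placebo.

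Section 12.2.8.1, in the text after Table LYDZ(b).3, fixes the method: "A Fisher’s Exact Test will be used to assess baseline smoking status as a predictor of" response and "strong response (a 40% decrease from baseline on the CAARS-Inv:SV total ADHD symptom score". If data are sparse, chi-squared may replace it.

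The full-scale analyses of CAARS-Inv:SV do not mention smoking:

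- Section 12.2.6 (primary MMRM): "The model will include the fixed, categorical effects of treatment, investigator, visit, and treatment-by-visit interaction", plus baseline score and baseline-by-visit.
- Section 12.2.7 (LOCF ANCOVA): baseline, treatment and investigator.
- Section 12.2.10: "Subgroups of patients for efficacy analyses will include investigational site, prior- stimulant-use strata, ADHD subtype, gender, and age". This section calls for models that test treatment-by-subgroup interaction, and spells out an ANCOVA on the total score for site.

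Section 12.2.1 sets 0.05 two-sided for treatment effects and 0.10 for interaction effects. The protocol gives no smoker share, responder rate, smoking effect or power for this objective.

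**The concern.** The total score has 18 items rated 0 to 3, so it runs from 0 to 54. It is rated at every visit and analysed on its full scale for the treatment comparison. The other response cuts in Table LYDZ(b).3 have a full-scale partner: the MMRM for CAARS-Inv:SV and an ANCOVA for CGI-ADHD-S. The smoking question has none.

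A difference in treatment effect between smokers and non-smokers is hard to detect in a trial of this size. Discarding a third or more of the information makes it more likely that a real difference is missed and then read as smoking having no predictive value. This is a matter of outcome scale. It would remain if Fisher's test were replaced by an interaction test on the same yes/no outcome.

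**Working it through.** **Inputs from the protocol (section 12.1).** 440 patients, 1:1; 68% completion, so 0.68 × 220 = 149.6 per arm (about 299 in all); treatment effect 0.35 SD; LOCF figures of SD 10.0, difference 3.5 and power 85%. Two-sided 5% throughout unless stated.

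**Assumed, because the protocol is silent.** Smokers 20-40%; responder rate 20-50%; interaction (effect in smokers minus effect in non-smokers) of 0.35, 0.5 or 0.7 SD.

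**1. The plan's own figure.** Two groups of 149.6 and a difference of 0.35 SD give a power of about 86%, against 85% stated. It reproduces. The 90% stated for the MMRM cannot be recomputed without the covariance matrix. It lies between about 86% (completers only) and about 96% (all 220 per arm).

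**2. Information kept after a cut.** For a normal outcome and a modest effect, relative efficiency is φ(z)² / [r(1−r)], where r is the responder share and z its normal quantile.

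| Responder share | Efficiency | Equivalent of 440 |
|---|---|---|
| 50% | 0.637 | 440 × 0.637 = 280 |
| 30% | 0.576 | 440 × 0.576 = 253 |
| 20% | 0.490 | 440 × 0.490 = 216 |

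This step does not need an assumed interaction size. No cut keeps more than about 64%.

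**3. Interaction power.** With 440 patients and 30% smokers there are 220 × 0.30 = 66 smokers and 154 non-smokers per arm. The standard error of the interaction is √(2/66 + 2/154) = 0.208 SD. Full-scale power is Φ(δ/0.208 − 1.96). On the cut, δ/0.208 is multiplied by the square root of the efficiency. For δ = 0.35, δ/SE = 1.68 and full-scale power is 39%. At a 50% share it becomes 1.68 × √0.637 = 1.34, and power is 27%.

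| Patients, 30% smokers | Interaction | Full scale | Cut, share 50% / 30% / 20% | Loss (points) |
|---|---|---|---|---|
| 440 | 0.35 SD | 39% | 27 / 25 / 22% | 12 / 14 / 17 |
| 440 | 0.5 SD | 67% | 48 / 45 / 39% | 19 / 23 / 28 |
| 299 | 0.35 SD | 28% | 20 / 18 / 16% | 9 / 10 / 12 |
| 299 | 0.5 SD | 51% | 35 / 32 / 28% | 16 / 18 / 22 |

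**4. Whole grid.** Simulation used four cells (arm by smoking), with the cut placed to give placebo response of 20, 35 or 50%, smokers at 20, 30 or 40%, and 300 or 440 patients. A full-scale contrast was compared with a difference of log odds ratios. The losses were about 9-20 points at 0.35 SD and about 15-31 points at 0.5-0.7 SD. For 0.35 SD the formula in step 3 gives 10-20 points at 440 patients and 7-14 at 299 (smokers 20-50%).

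**5. Size of the assumed interactions.** With 30% smokers and an average effect of 0.35 SD, the effect in non-smokers is 0.35 − 0.30δ.

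- δ = 0.35: 0.245 in non-smokers, 0.595 in smokers.
- δ = 0.5: 0.20 and 0.70.
- δ = 0.7: 0.14 and 0.84.

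**6. At the 0.10 interaction level.** For 440 patients, 30% smokers and 0.35 SD, full-scale power is Φ(1.68 − 1.645) = 51%. On the cut at a 30% share it is Φ(1.28 − 1.645) = 36%. The gap is of similar size.

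**7. Fisher's test inside one arm.** Smokers were compared with non-smokers among 150 or 220 atomoxetine patients, with a smoker share of 20-50% and an effect of 0.35 or 0.5 SD. Simulated loss against a t-test was about 15-38 points.

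**The case against.** The strongest reply is that the test fits the objective. Section 6.2.3 asks about response and strong response, and section 12.2.8.1 tests those two outcomes. A reader might infer from the missing full-scale analysis that the two sections conflict. They do not. A difference in mean points is also a different quantity from a difference in response probability: interaction depends on scale, and the cuts are on percent decrease. That argument stands. It rules out treating the responder analysis as an error to be removed, but not adding a full-scale analysis beside it.

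A reader might also take 15-31 points as the plain cost. The documents do not support that. That range needs interactions of 0.5-0.7 SD, larger than the whole treatment effect of 0.35 SD. At 0.35 SD the loss is smaller and full-scale power is itself only about 23-44% on the grid, so a null result would say little either way. Steps 3 and 4 also price an interaction test on the cut outcome, which is not the planned Fisher test.

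Nor may one say that CAARS-Inv:SV lacks a full-scale analysis: sections 12.2.6 and 12.2.7 provide two. Only smoking as a predictor lacks one.

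Finally, the lists in sections 12.2.8.1 and 12.2.10 are open-ended, and section 12.2.1 allows exploratory analyses. This is true, but an optional exploratory analysis is not a pre-specified one for a named objective whose method the protocol has already chosen.

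**Conclusion.** The point holds as an inefficiency. A named objective is tied to two cuts of a score that is available in full at every visit, and no full-scale analysis with smoking is specified. The firm part of the size is the information kept: at most about 64%, and about 49% at a 20% responder share, given a roughly normal score. The power loss is conditional on the assumptions in the working: about 9-20 points for a 0.35 SD interaction and about 15-31 points for 0.5-0.7 SD. The objective is secondary, outside the gated sequence and unpowered. The primary analysis is untouched. This is a worthwhile cheap improvement and no more.

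**What to change.** - In section 12.2.10, add baseline smoking status to the subgroup factors.
- In section 12.2.8.1, pre-specify a treatment-by-smoking contrast at Visit 6 on the CAARS-Inv:SV total score. Use the primary MMRM with smoking, treatment-by-smoking, smoking-by-visit and treatment-by-smoking-by-visit terms added, judged at the 0.10 interaction level already in section 12.2.1.
- Keep the 25% and 40% response results by arm and smoking status alongside it, because they answer the objective as worded in section 6.2.3.

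The cost is one extra model and some wording. No new patients or procedures are needed: the score is rated at every visit, and the schedule already has cotinine at Visit 1 and the Fagerstrom test and Timeline Followback at Visit 2. The downside is a result in points that must be read next to the responder rates, and the two may differ.

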**12.2. Statistical and Analytical Plans**

***12.2.1. General Considerations***

Statistical analysis of this study will be the responsibility of Eli Lilly and Company or an approved vendor of Eli Lilly and Company.

Treatment effects for all efficacy and safety variables will be evaluated based on a two- sided significance level of 0.05, and the interaction effects at 0.10. Any change to the data analysis methods described in the protocol will require an amendment ONLY if it changes a principal feature of the protocol. Any other changes in the data analysis methods described in this protocol will be documented in the Statistical Analysis Plan (SAP) prior to unblinding of the data. Such changes will not require protocol amendments. If changes to the data analysis methods described in the protocol are deemed necessary the justification for making such changes will be described in the clinical study report. Additional exploratory analyses of the data will be conducted as deemed appropriate.

Active treatment phase refers to the visit interval after randomization in which the placebo lead-in period is excluded. In all the analyses, baseline will be the latest non- missing observation across all the visits in the screening phase and the placebo lead-in period, before the active study drug begins. Endpoint will be the latest non-missing observation across all the post-baseline visits before.

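### The smoking analysis asks a treatment-by-smoking question but plans only a Fisher's exact test, and its sparse-data switch to chi-squared runs the wrong way

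*Protocol*

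**What the plan says.** The last bullet of Protocol Section 6.2.3 sets the objective: "To assess baseline smoking status as a predictor of response" and strong response (falls of 25% and 40% on the CAARS-Inv:SV total), "to atomoxetine treatment compared with placebo".

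The matching analysis is the last paragraph of Section 12.2.8.1, after Table LYDZ(b).3: "A Fisher’s Exact Test will be used to assess baseline smoking status as a predictor of response", with the same comparative ending. It does not say which 2×2 table is meant and names no stratified, homogeneity or interaction test. It closes with the fallback: "If sparse data exists, a Chi-Squared analysis may be used instead".

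Two other places bear on this:
- Section 12.2.1 sets test levels: a two-"sided significance level of 0.05, and the interaction effects at 0.10".
- Section 12.2.10 plans "statistical models that test for subgroup effects and treatment by subgroup interaction". Its efficacy subgroups are site, prior stimulant use, ADHD subtype, gender and age. Smoking is not among them.

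**The concern.** The objective involves three factors: smoking, treatment and response. Predicting response to drug relative to placebo means that the treatment effect differs between smokers and non-smokers. A Fisher test sees two factors at a time. It can therefore report a general prognostic factor as a predictor of drug benefit, or miss a real modifier.

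The fallback also points away from the safer test. Pearson's chi-squared relies on a large-sample approximation that weakens as expected counts fall. Fisher's test is conditional and exact, so its level does not depend on large counts.

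What is at stake is a possible claim about which patients benefit from atomoxetine, which the Protocol's Introduction describes as very pertinent to prescribers.

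**Working it through.** **Inputs.** From the Protocol: 220 per arm and 68% completion (Section 12.1), so 0.68 × 220 ≈ 150 completers per arm; levels of 0.05, and 0.10 for interactions (Section 12.2.1). The Protocol gives no smoker share, no response rate by smoking status, and no power or error rate for this analysis, so there is no stated figure to reproduce. Assumed: 30% smokers (66 smokers and 154 non-smokers per arm), 20-40% for power, and the response rates shown below.

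**1. Does a Fisher test reach the question?** The hypothesis of no modification is that the interaction odds ratio equals 1, where

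interaction OR = (atomoxetine/placebo OR in smokers) ÷ (atomoxetine/placebo OR in non-smokers).

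Two constructed data sets, as responders/patients:

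| | Example A: prognostic only | Example B: modifier |
|---|---|---|
| Atomoxetine: smokers, non-smokers | 46/66, 77/154 | 43/66, 77/154 |
| Placebo: smokers, non-smokers | 33/66, 46/154 | 23/66, 77/154 |
| Interaction OR | 2.30 ÷ 2.35 = 0.98 | 3.50 ÷ 1.00 = 3.50 |
| Interaction p (likelihood ratio) | 0.96 | 0.003 |
| Fisher, smoking × response, pooled | 0.0002 | 1.00 |
| Fisher, smoking × response, atomoxetine; placebo | 0.008; 0.006 | 0.040; 0.040 (opposite directions) |
| Fisher, treatment × response, smokers; non-smokers | 0.033; 0.0005 | 0.0009; 1.00 |

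In A, the smoking tests are clearly significant although smoking does not modify the treatment effect. In B, the pooled test sees nothing although it does. The stratum tests give two p-values and no test of their difference.

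**2. If the two within-arm tests were compared.** Let a and b be the exact powers of Fisher's test in the two arms. Then P(disagree) = a(1−b) + b(1−a), and P(significant on atomoxetine only) = a(1−b). Smokers respond less often by the same number of points in both arms. Non-smokers respond at 50-60% on atomoxetine and 30-45% on placebo.

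| Deficit | Disagree | Atomoxetine only |
|---|---|---|
| 5 points | 16-17% | 8% |
| 10 points | 37-40% | 16-18% |
| 15 points | 50% | 17-24% |
| 20 points | 28-35% | 6-15% |
| 25 points | 7-12% | under 1% to 4% |

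At 15 points, for example, a ≈ 0.50 and b ≈ 0.52 give 0.50 × 0.48 + 0.52 × 0.50 = 0.50. For two tests of equal power p, disagreement is 2p(1−p), which peaks at 50%. The comparator is a nominal 10% for an interaction test at 0.10.

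That comparison is only indicative, because a common deficit in points is not a common odds ratio. At 25 points the odds ratio is (0.25/0.75) ÷ (0.50/0.50) = 0.33 from a base of 50%, but (0.05/0.95) ÷ (0.30/0.70) = 0.12 from a base of 30%.

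**3. The fallback.** Exact size = Σ Bin(x; n₁, p) · Bin(y; n₂, p) over all tables that the test rejects at nominal 5%. The chi-squared has no continuity correction.

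| Smokers v non-smokers | Chi-squared maximum (at response rate) | Chi-squared at response 35-69% | Fisher maximum |
|---|---|---|---|
| 3 v 147 | 10.0% (4%) | 1.2-5.1% | 2.7% |
| 5 v 145 | 8.3% (3%) | 3.4-5.9% | 2.7% |
| 8 v 142 | 7.4% (2%) | 4.4-5.1% | 2.6% |
| 45 v 105 | 5.4% (10%) | 4.9-5.0% | 4.3% |
| 66 v 154 | 5.1% (28%) | 5.0-5.1% | 4.3% |

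Fisher never exceeds 5%. Chi-squared is accurate where counts are ample and uncontrolled where they are sparse.

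**4. Power of the direct test.** Assume response of 70% v 45% in smokers and 55% v 45% in non-smokers, so the interaction OR is 1.91 and its log is 0.647. With 220 per arm, SE = √Σ 1/[n·p(1−p)] over the four cells: 0.496 at 20% smokers and 0.402 at 40%. Power at 0.10 is Φ(0.647/SE − 1.645), which gives 37% and 49%.

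**The case against.** **Scale.** The inflated chi-squared sizes need both very few smokers and a response rate of 2-4%. A reader might infer that the fallback would give an anti-conservative p-value in this trial. The documents do not support that: at mid-range response rates even the sparse tables run at about 1-6%, and with 30% smokers sparse cells are unlikely. The sentence is also only permissive. This stands as a limit on size. It does not make the rule point the right way.

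**Reading.** A reader might also infer that the plan will compare significance between arms and be misled half the time. The Protocol never says that within-arm tests will be set against each other, and 50% is the ceiling of a range. This also stands, so step 2 shows the consequence of one possible reading only.

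**Detail left to the SAP.** A SAP may name the table, and Section 12.2.1 lets lesser method changes be made there. But the Protocol has already fixed the test and the fallback, and naming any of the three natural tables would not cure the mismatch. Treatment by smoking among responders alone would, under randomisation, address modification on the risk-ratio scale, but nothing in the text points to that table.

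**Importance.** The objective is ungated and unpowered, and the interaction test may well be inconclusive. That lowers the stakes. It does not justify a test of a different hypothesis.

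**Conclusion.** The point holds as a specification error of modest consequence. The mismatch between objective and test needs no assumed numbers: none of the pooled, within-arm or within-stratum Fisher tests addresses modification of the atomoxetine-placebo difference, and Section 12.2.10 does not fill the gap. The reversed fallback is likewise plain from the text.

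The sizes rest on assumed smoker shares and response rates:
- Chi-squared can reach 7-10% in extreme tables, but at most about 5.4% with 30% smokers.
- Within-arm tests, if compared, would disagree in about 7-50% of trials when smoking is purely prognostic. An atomoxetine-only finding would appear in under 1% to about 24%.

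The primary analysis and the gated AAQOL-29 sequence are untouched, and nothing here supports a wider doubt about the trial's efficacy conclusions.

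**What to change.** Delete the chi-squared sentence. For response and for strong response, replace the Fisher test with a logistic model containing treatment, baseline smoking status and their interaction. Test the interaction at the 0.10 level that Section 12.2.1 already sets. State that modification is judged on the odds-ratio scale, and report the treatment effect with its confidence interval in smokers and in non-smokers. If cells are sparse, use an exact method, for example an exact test of homogeneity of odds ratios.

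The cost is two sentences and no new data. Section 12.2.1 allows such a change to be documented in the SAP before unblinding, without an amendment, provided it is not a principal feature. The real cost is power: about 37-49% under the effect assumed above. The text should therefore say in advance that a non-significant interaction is inconclusive and is not evidence that smoking status does not matter.
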